**Table 2 T2:**
[figure not shown]
Modified Mayo score system for assessment of ulcerative colitis activity.

Minor outcomes including individual symptom score, TCM syndrome score, endoscopic response rate, mucosal healing rate, and quality of life scale score.

1.Individual symptom score: referred Guidance Principle of Clinical Study on New Drug of Traditional Chinese Medicine.^[17]^ All symptoms were divided into four levels: none, mild, moderate, and severe. The main symptoms were scored as 0, 2, 4, and 6 points, and the minor symptoms are scored as 0, 1, 2, and 3 points. The tongue and pulse were divided into normal and abnormal grades, 0 and 2 points were recorded in the main symptom, and 0 and 1 points were recorded in the minor symptom.2.TCM syndrome score: The score was graded based on the degree of individual symptom score. All indicators were determined by comparing the values obtained at 2, 4, and 8 weeks with baseline values.Clinical recovery: clinical symptoms disappeared or syndrome score decreased by ≥95% from the baseline;Marked efficacy: the syndrome score decreased by ≥70% and <95% compared with the baseline;Efficacy: the syndrome score was a decrease of at least 30% and less than 70% from the baseline;Invalid: the syndrome score was a decrease of less than 30% from the baseline;Worsen: the syndrome score exceeded the baseline after treatment.TCM syndrome efficacy rate = (Clinical recovery + Marked efficacy + Efficacy) cases /a total number of cases ×100%.Endoscopic response rate: was defined as endoscopic score decreased at least 1 point from the baseline in the modified Mayo score. Endoscopic response rate = endoscopic response cases / total number of the group ×100%.(2)Mucosal healing rate: was defined as absolute subscore for endoscopy of 0 or 1. Mucosal healing rate = Mucosal healing cases / total number of the group ×100%.(3)Quality of life assessment: Patients were evaluated by Inflammatory Bowel Disease Questionnaire,^[18]^ included the 32 most frequent and important items. Inflammatory Bowel Disease Questionnaire was divided into 4 modules: bowel symptoms (10 questions), systemic symptoms (5 questions), emotional function (12 questions), and social function (5 questions). Each question has graded responses from 1 to 7, and thus the total score is ranging from 32 to 224, with higher scores representing a better quality of life.

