### Eligibility criteria

2.5

Diagnostic criteria:

1.The western medicine diagnostic criteria of UC will refer to Chinese consensus on diagnosis and treatment of IBD (Beijing, 2018).^[14]^2.The TCM diagnostic criteria of the damp-heat stasis blocking and spleen-qi deficiency syndrome will refer to the Clinic terminology of traditional Chinese medical diagnosis and Consensus of traditional Chinese medical in diagnosis and treatment of UC.^[15,16]^ Diagnosis of this syndrome including the main and minor symptoms as following:

Main symptoms:

1.Diarrhea, mucus and bloody stools;2.Abdominal pain;3.Tesmus;4.Tired and lazy;

Minor symptoms:

1.burning anus;2.short and dark-color urine;3.dry and bitter in the mouth;4.drowsiness of limbs;5.poor appetite.

Tongue and pulse: red tongue, thick yellow fur with tooth marks on the sides, and smooth pulse.

Confirmation of the syndrome type: 2 main symptoms (required for the first item) plus 2 minor symptoms, which can be diagnosed by referring to the tongue and pulse.

Inclusion criteria:

1.Diagnosed with active UC.2.Defined by modified Mayo score of 3 to 5 points (mild period).^[14]^3.Differentiation of TCM syndrome is damp-heat stasis blocking accompanied with spleen-qi deficiency.4.Age >18 and <65 years.5.Voluntary to participate and providing written informed consents, as required by Good Clinical Practice.

Exclusion criteria:

1.Patients during remission period, moderate or severe period.2.Pregnancy, lactation, or have desire for pregnancy.3.Severe allergy or allergic to mesalazine or any of the ingredients in HEC.4.Have cardiovascular, pulmonary, liver, renal, endocrine, nerve, and hematology diseases. Blood creatinine level, blood alanine transaminase or aspartate aminotransferase level above the upper limit of normal.5.Have serious complications, such as intestinal stenosis, intestinal obstruction, intestinal perforation, multiple intestinal polyps, toxic megacolon or colorectal cancer, etc.6.Mental disorders or other causes which result in inability of proper expression of feelings.7.Have participated in other medical clinical studies in the last 3 months.8.In addition to mesalazine, receiving other treatments for UC.9.Serious and unstable condition requiring emergency treatment.10.Inappropriate to participate in this trial judged by clinical physicians.

Termination and withdrawal criteria:

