### Data analysis

3.7

Data analysis will be performed by professional statisticians and the main researchers using SPSS 22.0. Statistical analysis included the actual number of subjects selected, cases of shedding and rejection, demography and other baseline characteristics, patient compliance, efficacy and safety analysis. We used frequency tables or percentages for categorical variables, and mean ± standard deviation for continuous variables to describe the characteristics of patients in both groups. Categorical data will be analyzed by chi-square test or Fisher exact test to compare the differences between the 2 groups, while quantitative data with normal distribution will be analyzed by *t* test. If the data does not conform to the normal distribution or the uniformity of variance, Wilcoxon rank sum test or Wilcoxon signed test will be used to analyze them to compare the two groups. A two-sided *P-*value <.05 will be set as the significant level.

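### Eight of the nine individual symptom scores may include patients with no symptom at baseline; unadjusted whole-group tests would then be valid but diluted and short of power

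*Protocol article*

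**What the plan says.** All of this is in the protocol article.

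- **Entry (Section 2.5).** The TCM syndrome is an inclusion criterion: "Differentiation of TCM syndrome is damp-heat stasis blocking accompanied with spleen-qi deficiency". There are four main and five minor symptoms, and the syndrome is confirmed by "2 main symptoms (required for the first item) plus 2 minor symptoms, which can be diagnosed by referring to the tongue and pulse". The first main symptom (diarrhea, mucus and bloody stools) is therefore compulsory; none of the other eight is.
- **Outcome (Section 3.4).** The symptom score is secondary: "Minor outcomes including individual symptom score, TCM syndrome score, endoscopic response rate, mucosal healing rate, and quality of life scale score".
- **Scale (Section 3.4).** "All symptoms were divided into four levels: none, mild, moderate, and severe", and "The main symptoms were scored as 0, 2, 4, and 6 points, and the minor symptoms are scored as 0, 1, 2, and 3 points". A patient without the symptom scores 0.
- **Timing (Section 3.4, under the TCM syndrome score).** "All indicators were determined by comparing the values obtained at 2, 4, and 8 weeks with baseline values".
- **Test (Section 3.7).** "quantitative data with normal distribution will be analyzed by" a t test, with a Wilcoxon test if the data are not normal or the variances differ, at a two-sided 0.05 level. These are general tests for all quantitative outcomes. The article mentions no baseline adjustment, and it does not say which patients enter each symptom comparison.

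**The concern.** A patient who starts at 0 on a symptom cannot improve on it. If such patients are included, they add near-zero changes to both arms. The mean difference between arms then describes symptom relief averaged over people with and without the symptom, and it moves toward zero as the symptom becomes less common.

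The named tests also leave the spread in baseline scores (0 against 2, 4 or 6) in the error term, which costs further power.

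What is at stake is how the symptom-level results are read. A real advantage or deficit of HEC on, say, abdominal pain or tenesmus could appear as a small, non-significant difference. A reader of an active-controlled trial might take that as similarity between the treatments.

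**Working it through.** **The plan's own figure.** The only sample-size figure is 120 per group. With P1 = 0.8311, P2 = 0.68 and P = 0.7556 (Section 2.3):

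n = (1.645 + 0.842)² × 2P(1 − P) / (P1 − P2)² = 100.07, and 100.07 × 1.2 = 120.1.

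This reproduces 120, but it is sized on the efficacy rates. The article gives no power, effect or SD for the symptom scores.

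**Step 1: what the entry rule guarantees.**

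- First main symptom: present in 100%, so no dilution.
- Main symptoms 2 to 4: at least 1 of 3, so prevalence averages at least 1/3.
- Minor symptoms: at least 2 of 5, so prevalence averages at least 40%.

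These floors are averages across symptoms, reached only if every patient just meets the rule. Actual prevalence is not given.

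**Step 2: dilution, without assuming an effect size.** If a share q has the symptom and the rest stay at 0 in both arms:

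whole-group difference = q × difference among patients with the symptom.

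At the floors this is about 33% and 40% of the difference among those with the symptom.

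**Step 3: power by closed form (assumed effect).** Assume mean improvements of 2.0 and 1.2 points among patients with the symptom (difference 0.8), SD 2.0, no change in the others, and 120 per arm. The variance of the whole-group change in an arm with mean m is q(SD² + m²) − (qm)². At q = 0.4:

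- 0.4(4 + 4) − 0.8² = 2.56
- 0.4(4 + 1.44) − 0.48² = 1.95
- pooled SD = √2.25 = 1.50

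| q | Difference, all | Power, all | Power, symptom present |
|---|---|---|---|
| 1.0 | 0.80 | 87% | 87% |
| 0.8 | 0.64 | 74% | 79% |
| 0.6 | 0.48 | 57% | 67% |
| 0.4 | 0.32 | 38% | 50% |

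**Step 4: power by simulation, separating adjustment from restriction.** Assumptions, none from the article:

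- main-symptom scoring, 120 per arm;
- patients with the symptom are 70% mild (2 points) and 30% moderate (4 points);
- mild symptoms resolve in 50% against 75%;
- moderate symptoms resolve fully at 60% of those rates (30% against 45%);
- new onset is 3% in both arms.

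The difference among patients with the symptom is 0.7 × 2 × 0.25 + 0.3 × 4 × 0.15 = 0.35 + 0.18 = 0.53 points. At prevalence 1/3 the whole-group difference is 0.53/3 = 0.18.

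| Prevalence | Named tests, whole group | Baseline-adjusted, whole group | Baseline-adjusted, baseline above 0 |
|---|---|---|---|
| 1/3 | 23-27% | 34% | 43% |
| 0.7 | 55-66% | 72% | 76% |

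Repeating the simulation moves these figures by up to about 4 points. At prevalence 1/3, adjustment alone gains 34 − 27 = 7 to 34 − 23 = 11 points, and restriction adds 43 − 34 = 9. At 0.7, adjustment gains 72 − 66 = 6 to 72 − 55 = 17 points, and restriction adds 4.

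**The case against.** The strongest reply is that the article never says these are whole-group comparisons. Section 3.4 attaches the group total as denominator to the response rates, not to the symptom scores, and a condensed article may leave the analysis set of a secondary score to a fuller document. That stands: the point is conditional on a whole-group reading. It still has substance, because the article does fix the entry rule, a scale that includes 0, and tests without baseline adjustment.

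Several stronger readings are tempting, and the documents do not support them:

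- **Every symptom comparison is diluted.** The first main symptom is compulsory, so at most eight of nine are affected.
- **Prevalence is about 1/3 or 40%.** Those are floors. If most patients have the symptom, little is lost.
- **The whole-group test is wrong.** It keeps the randomised comparison and its error rate, and it captures new onset in patients starting at 0. It answers a different question with less power.
- **All the lost power comes from failing to restrict.** In the simulation at prevalence 1/3, roughly half comes from the absence of baseline adjustment.
- **The noninferiority conclusion is at risk.** Noninferiority sizing rests on the efficacy rates, and the article attaches no noninferiority claim to the symptom scores. Reading a non-significant symptom test as equivalence would be wrong under either analysis.

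**Conclusion.** The point holds in limited form. For up to eight of nine symptom scores, entry allows a baseline of 0, and the only tests named are unadjusted two-group tests. If applied to everyone, they are valid but estimate a difference shrunk roughly to the symptom's prevalence, and they give up power that a better analysis would keep.

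The size depends on prevalence, effect and severity mix, none of which the article states. In the illustration, the better analysis gains 43 − 27 = 16 to 43 − 23 = 20 points of power at prevalence 1/3, and 76 − 66 = 10 to 76 − 55 = 21 points at 0.7, where most of the gain comes from adjustment. The consequence is confined to one secondary outcome; the primary outcome and the total syndrome score are untouched.

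**What to change.** Add a short statement to the analysis section:

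1. Compare each individual symptom score between arms adjusted for its own baseline score.
2. Make the improvement comparison in patients whose baseline score for that symptom is above 0. This subset is defined before randomisation, so the comparison remains randomised.
3. Report new onset among patients starting at 0 separately, as a frequency by arm.
4. Show the number analysed per arm for each symptom.
5. Keep the total syndrome score on all patients.

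This needs no new data. Baseline adjustment costs nothing. Restriction gives each symptom a different and smaller number of patients, which is why those numbers must be shown.

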### Number of Samples

2.3

Number of Samples was determined based on the calculation of noninferiority trial design. The efficacy rates of EMT ranges from 65% to 71%,^[12,13]^ and the average rate is about 68%. Our previous study found that the efficacy rates of HEC is 83.11% in treating MAUC. The sample size was calculated by the following formula: 

*U*α, *U*β is the corresponding *U* value of α, β. When α equaling to 0.05, β equaling to 0.1, *U*α (0.05) is 1.645, *U*β (0.2) is 0.842. *P*_1_ and *P*_2_ represent the efficacy rates of HEC and EMT. *P* equals to (*P*_1_ + *P*_2_) /2 × 100%. The certainty was set at 80%, considering 20% of sample lose. The sample number was set to 120 for each group, 240 in total, and 40 samples in each center.

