1.The participant is not willing to continue the clinical trial.2.No medication or any follow-up records;3.Important deviations occur in the process of the clinical trial, such as poor compliance.4.Occurrence of allergic reactions or serious adverse events during the trial.5.Not alleviated or the symptoms are aggravated.

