### Follow-up

3.3

Each patient was provided with a participant diary card to record diary signs and symptoms of diarrhea, mucilage or blood–pus stools, abdominal pain, and tenesmus. Patients will be interviewed every 2 weeks after enrollment in the trial, while they should return the remaining drugs and packages, and receive the drugs they need to take for the next 2 weeks. Assessment of study endpoints and duration of follow-up was shown in Figure 2.

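### The TCM syndrome score is taken at baseline and weeks 2, 4 and 8, but section 3.7 names only two-sample tests without baseline or centre adjustment; a repeated-measures model would be more precise and less exposed to outcome-related loss

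*Protocol article*

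**What the plan says.** - **Measurement (section 3.4, minor outcomes).** For the TCM syndrome score, "All indicators were determined by comparing the values obtained at 2, 4, and 8 weeks with baseline values". The score is also graded into categories, with "TCM syndrome efficacy rate = (Clinical recovery + Marked efficacy + Efficacy) cases /a total number of cases ×100"%.
- **Visits (section 3.3).** "Patients will be interviewed every 2 weeks after enrollment in the trial".
- **Analysis (section 3.7).** For two-group comparisons, "quantitative data with normal distribution will be analyzed by" a t test. Otherwise a "Wilcoxon rank sum test or Wilcoxon signed test will be used to analyze them to compare the two groups". "Categorical data will be analyzed by chi-square test or Fisher exact test to compare the differences between the 2 groups". No model with covariates and no repeated-measures method is named.
- **Loss.** Section 2.3 sets the sample size "considering 20% of sample lose". The termination and withdrawal criteria in section 2.5 include "Not alleviated or the symptoms are aggravated".
- **Randomisation (section 2.6).** The sequence is stratified by centre.

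**The concern.** Each test in section 3.7 compares the arms on one value per patient, either a score or a change from baseline. For a score with a baseline and three later measurements this has two costs.

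1. **Precision.** Subtracting baseline is less efficient than adjusting for it, and the centre strata are left out of the comparison.
2. **Outcome-related loss.** A patient withdrawn for lack of improvement may have week-2 and week-4 scores that predict the missing week-8 value. A week-8 test on observed values cannot use them. If loss differs between arms, the remaining patients no longer represent the randomised groups.

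The second cost is not reliably conservative. Section 2.2 declares a non-inferiority design. If the experimental arm were truly worse and lost more non-improvers, shrinkage toward zero would make the arms look more alike than they are.

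**Working it through.** **The plan's own figure.** Section 2.3 gives 120 per group. With P1 = 0.8311, P2 = 0.68, P = 0.75555, Uα = 1.645 and Uβ = 0.842, the usual pooled formula gives

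n = 2 × 0.75555 × 0.24445 × (1.645 + 0.842)² / (0.8311 − 0.68)² = 100.07,

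and 100.07 × 1.2 = 120.1, which matches. This rests on the primary efficacy rates. The article gives no SD, correlation or effect for the syndrome score, so everything below is assumed apart from n and the loss allowance.

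**Step 1: effect of baseline adjustment alone.** With unit SD, 120 × 0.8 = 96 patients per arm at week 8, a true difference of 0.40 SD, and loss unrelated to outcome:

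- SE = √(2v/96); power = Φ(0.40/SE − 1.96).
- Change score: v = 2(1 − ρ). Baseline-adjusted: v = 1 − ρ². Here ρ is the baseline to week-8 correlation.

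| ρ | Method | v | SE | 0.40/SE | Power |
|---|---|---|---|---|---|
| 0.4 | change-score t test | 1.20 | 0.158 | 2.53 | 72% |
| 0.4 | baseline-adjusted | 0.84 | 0.132 | 3.02 | 86% |
| 0.6 | change-score t test | 0.80 | 0.129 | 3.10 | 87% |
| 0.6 | baseline-adjusted | 0.64 | 0.115 | 3.46 | 93% |

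Baseline adjustment alone gives 6 to 14 points.

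**Step 2: loss related to observed change.** This simulation used a true difference of 0.40 SD, correlations of 0.4 to 0.7 and about 18-22% loss depending on the change already observed.

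| Method | Estimate | Power |
|---|---|---|
| change-score t test, observed week-8 values | 0.37-0.39 | 69-87% |
| baseline-adjusted, observed week-8 values | 0.39-0.40 | 83-93% |
| likelihood-based, all visits | 0.40 | 86-95% |

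Shrinkage of the first row is 1 − 0.39/0.40 to 1 − 0.37/0.40, or about 3-7%. Between the first and third rows power rises by roughly 8-18 points. Between the second and third, which isolates the early visits, it rises by about 1-4.

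**Step 3: a common withdrawal threshold.** A separate simulation used 120 per arm and 20% overall loss after week 4, with one threshold on week-4 change for both arms. The strict rule removes the 20% of patients with least improvement. The loose rule removes half of the 40% with least improvement. Decaying correlation means 0.9 per week.

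| Correlation | Rule | True | Completers | Shrinkage | All visits |
|---|---|---|---|---|---|
| 0.6 throughout | loose | 0.50 | 0.477 | 5% | 0.496 |
| 0.6 throughout | strict | 0.50 | 0.440 | 12% | 0.501 |
| decaying | loose | 0.50 | 0.469 | 6% | 0.499 |
| decaying | strict | 0.50 | 0.399 | 20% | 0.501 |
| 0.6 throughout | loose | 0.30 | 0.288 | 4% | 0.298 |
| 0.6 throughout | strict | 0.30 | 0.266 | 11% | 0.303 |
| decaying | loose | 0.30 | 0.285 | 5% | 0.302 |
| decaying | strict | 0.30 | 0.236 | 21% | 0.301 |

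**Step 4: direction.**

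| True difference | Who leaves | Completers | All visits |
|---|---|---|---|
| 0 | common rule, both arms | 0.00 | 0.00 |
| 0.50 | non-improvers, 20% of each arm | 0.497 | 0.498 |
| 0.50 | control non-improvers only (36%) | 0.254 | 0.499 |
| 0.50 | experimental non-improvers only (36%) | 0.747 | 0.504 |

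The first row needs the same rule in both arms. With no true difference and non-improvers leaving one arm only, the completer difference is 0.24 in one direction or the other.

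**The case against.** Four stronger readings are tempting, and the article does not support them.

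- **That the early scores go unused.** Section 3.4 has them compared with baseline, so they may be tested at their own visits. They fail to inform the week-8 comparison only if missing values are not imputed.
- **That the week-8 difference will be underestimated.** Step 4 shows that the direction depends on which arm loses more non-improvers. The 20% in section 2.3 is a general allowance that is not tied to the withdrawal criterion. Section 2.5 gives that criterion no timing, and does not say whether a final assessment is made at withdrawal.
- **That t and Wilcoxon are the only tests for this outcome.** The graded efficacy rate is categorical and goes to chi-square or Fisher. If withdrawn patients stay in its denominator as failures, the loss mechanism described here does not apply to that rate.
- **That the early visits bring a large power gain.** Steps 1 and 2 show that most of it comes from baseline adjustment.

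A fair objector would add that the article never restricts the tests to completers, that analysis sets and missing-data rules commonly sit in a statistical analysis plan that is not shown, and that two-sample tests on a secondary score are valid. All of this stands, and the absence of a missing-data rule is no part of this point. What remains is that section 3.7 does name its methods, and those methods fit poorly with the measurement schedule, the stratification and the withdrawal criterion in the same article. An analysis plan that follows section 3.7 would carry the mismatch over.

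**Conclusion.** The point holds as a recommended improvement to a secondary analysis. It is not an error that invalidates the trial. Under the assumed values, an unadjusted week-8 change-score test gives up roughly 8-18 points of power and shrinks the estimate by about 3-7%, reaching about 20% only under a strict common threshold with decaying correlation. The bias is toward zero if the arm doing worse loses more non-improvers and away from zero if the better arm does. It is absent or negligible when equal fractions of non-improvers are lost, or when there is no true difference and one rule governs both arms. The all-visit estimate is unbiased in these runs because loss was made to depend only on observed scores. If loss depends on unseen scores, that protection is not assured.

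**What to change.** In section 3.7, for the continuous TCM syndrome score, replace the visit-by-visit two-sample tests with one mixed model for repeated measures:

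- Fixed terms: arm, week, arm-by-week, baseline score and centre.
- Unstructured covariance across weeks 2, 4 and 8.
- All randomised patients with at least one post-baseline score.
- Result to report: the week-8 arm contrast with its 95% confidence interval.

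Add one sensitivity analysis for departures from missing at random, since the model relies on that assumption; this is the small downside. Keep the graded efficacy rate as a separate categorical analysis. Extend the model to other scores only where the visit schedule confirms that they are taken at weeks 2 and 4, because the abstract speaks of assessment at baseline and trial end only and the schedule figure is not available here.

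The cost is analysis wording and one extra sensitivity run. No new visits, data or patients are needed.

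### The endoscopic response rate counts any patient who enters with an endoscopy subscore of 0 as a non-responder, because the denominator is the whole group and entry sets no endoscopic minimum

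*Protocol article*

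**What the plan says.** In section 3.4 (Outcomes), among the minor outcomes, endoscopic response requires that the "endoscopic score decreased at least 1 point from the baseline in the modified Mayo score". The rate is "Endoscopic response rate = endoscopic response cases / total number of the group ×100"%, with no condition on the baseline endoscopy subscore. The mucosal healing definition in the same list, which "was defined as absolute subscore for endoscopy of 0 or 1", shows that the endoscopy subscore can take the value 0.

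In section 2.5 (Eligibility criteria), severity is "Defined by modified Mayo score of 3 to 5 points (mild period"). The other relevant rules are "Diagnosed with active UC" and the exclusion of "Patients during remission period, moderate or severe period". None of these states an endoscopic floor.

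The outcome is secondary. It stands in the list "Minor outcomes including individual symptom score, TCM syndrome score, endoscopic response rate, mucosal healing rate, and quality of life scale score".

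**The concern.** A subscore of 0 cannot fall by a point. A patient who starts there is a fixed non-responder in either arm, yet stays in the denominator. Such a patient carries no information on whether either drug improves the mucosa. The absolute difference between arms is diluted and power is lost.

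The trial enrols mild disease only, which is where low endoscopy subscores are most plausible. The Discussion also names the lack of enteroscopy as a shortcoming of the previous trial of this product, so the endoscopic outcomes are part of what this trial is meant to add.

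The problem is separate from mucosal healing. There a low baseline subscore can count as success without any change; here a baseline of 0 is automatic failure. Adjusting the healing definition would leave this rate as it is.

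**Working it through.** **The plan's own figure.** The article gives no rate, power or sample size for endoscopic response. Its one sample-size figure is 120 per group (section 2.3), based on the clinical efficacy rate. The formula is not shown in the text, but the usual two-proportion form with the printed values reproduces the figure: P1 = 0.8311, P2 = 0.68, P = 0.75555, U values 1.645 and 0.842, so n = 2P(1 − P)(1.645 + 0.842)² / (0.1511)² = 100.07, and 100.07 × 1.2 = 120.1. It is used below only as the group size.

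**Can a patient with endoscopy 0 enter?** The article's only definition of remission (section 3.4, clinical remission) is a score of at most 2 with no subscore above 1. A total of 3 to 5 is not remission on that definition, even with endoscopy 0. Table 2 is not shown. If the score has four items of 0 to 3 (assumption), 91 item patterns total 3 to 5, with endoscopy subscore 0, 1, 2 and 3 in 34, 28, 19 and 10 of them. This shows that entry with endoscopy 0 is possible; it is not a prevalence.

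**Effect on the rate.** Let q be the share with baseline subscore 0, equal in both arms, and let pE and pC be the response rates among patients with baseline subscore of at least 1 in the experimental and control groups.

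- Whole-group rates: (1 − q)pE and (1 − q)pC.
- Risk difference: (1 − q)(pE − pC).
- Risk ratio: pE / pC, unchanged.

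**Size.** Inputs: 120 per arm (section 2.3) and two-sided 0.05 (section 3.7). Assumed, because the documents give neither: pE = 70%, pC = 55%, and q from 0 to 30%. Power uses the normal approximation for two proportions, Φ[(d − 1.96·se0)/se1], with d the difference, se0 the pooled and se1 the unpooled standard error. The whole-group version has n = 120 and rates multiplied by (1 − q). The at-risk version has n = 120(1 − q) and unscaled rates.

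Example, q = 20%:

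- Whole group, 56% v 44%, n = 120: d = 0.12, se0 = √(2 × 0.25/120) = 0.0645, se1 = √(0.4928/120) = 0.0641, power 46.0%.
- At risk, 70% v 55%, n = 96: d = 0.15, se0 = √(2 × 0.2344/96) = 0.0699, se1 = √(0.4575/96) = 0.0690, power 57.5%.

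| q | Whole-group difference (points) | Risk ratio | Power, whole group | Power, at risk |
|---|---|---|---|---|
| 0 | 15.0 | 1.27 | 67.2% | 67.2% |
| 2% | 14.7 | 1.27 | 64.9% | 66.3% |
| 5% | 14.25 | 1.27 | 61.4% | 64.9% |
| 10% | 13.5 | 1.27 | 55.9% | 62.6% |
| 20% | 12.0 | 1.27 | 46.0% | 57.5% |
| 30% | 10.5 | 1.27 | 37.4% | 51.9% |

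At every q above 0 in the table the at-risk denominator has more power, although it uses fewer patients.

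**Unequal shares.** With 5% at baseline 0 in the experimental group and 10% in the control group, the difference is 0.70 × 0.95 − 0.55 × 0.90 = 17.0 points. With the shares reversed it is 0.70 × 0.90 − 0.55 × 0.95 = 10.75 points.

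**The case against.** **The affected patients may be few or absent.** No passage says that anyone enters with endoscopy 0. Active disease is required under a consensus that is not shown, remission is excluded, and diarrhoea with mucus and bloody stools is the compulsory main symptom of the required TCM syndrome. All this makes an endoscopy subscore of 0 less likely. This stands as a limit on size: at q = 2% the power loss is 1.4 points and at q = 0 there is none. It does not remove the gap, because none of these rules excludes such a patient by its wording.

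**The whole-group denominator is conventional.** Section 3.4 also uses it for clinical efficacy, remission and mucosal healing. This stands too. The whole-group rate describes all randomised patients, and its difference is a diluted quantity, not a biased estimate.

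**Stronger readings.** A reader might infer that any true difference between the arms is pulled toward zero. The documents do not support that: there is no dilution at q = 0, the risk ratio never changes, and a chance imbalance in q can widen the difference as well as narrow it. Under randomisation that imbalance is part of ordinary sampling variation. A reader might also infer that, since section 2.2 declares a noninferiority design, the definition raises the chance of a false noninferiority claim by a calculable amount. That would need a margin and a noninferiority test for this outcome. The article states no margin, and section 3.7 gives only chi-square or Fisher tests of difference.

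**It could be left to the analysis plan.** A supplementary subset analysis could be. Here, however, the article itself fixes both numerator and denominator, so the definition can be judged as it stands.

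**Conclusion.** The point holds as a conditional weakness in a secondary outcome. The definition and the entry criteria together allow patients who cannot respond, and count them as failures. If they enter in equal shares q, the expected risk difference is multiplied by (1 − q) and the risk ratio is unchanged. Under the assumed 70% v 55% with 120 per arm, the cost against an at-risk denominator is 1.4 power points at q = 2%, 3.5 at 5%, 6.7 at 10%, 11.5 at 20% and 14.5 at 30%. The cost is small at low q and matters only if q is sizeable. The response rates and q are assumptions; the documents give neither, and q may be 0. The primary outcome is untouched.

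**What to change.** In section 3.4, or in the analysis plan before unblinding, define the endoscopic response rate as the number of patients with a fall of at least 1 point divided by all randomised patients in the group whose baseline endoscopy subscore is 1 or more. Report the number with baseline subscore 0 by arm, and keep the whole-group rate as a supplementary figure. The restriction uses a baseline value only, so the comparison stays randomised.

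The cost is one sentence and no new data. The small downside is that this rate then describes only patients with visible inflammation at entry. If no patient has baseline subscore 0, the two rates coincide and nothing is lost.
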